### Randomization and allocation of treatment

In crossover trials, both experimental and control experiments are given to every participant, randomizing the order in which they are applied
[65]. Consenting participants will be allocated treatment using a computer-generated simple block randomization. The benefits of using blocks are to ensure that the accrual of participants to either arm is uniform over time. An independent researcher, not involved in the recruitment or evaluation of follow-up, will prepare sealed, numbered envelopes containing an allocated treatment. Once randomization has occurred, blinding of participants and the caregiver is not feasible for this type of intervention, providing a potential risk for bias.

### Data analysis

The equivalence of the two groups will be checked using demographic variables such as age, marital status, occupation, level of education, cultural background, language, and child’s diagnosis. Differences between groups will be tested using chi-square and t-tests.

#### Hypotheses testing

We will carry out an ‘intent to treat’ analysis. That is, participants will remain in the group to which they were allocated or assigned, whether or not they are poor compliers with the TN intervention. Data will be summarized with the mean and SD; continuous variables will be tested for normality.

Data will be analyzed using mixed effect linear models to exclude any ‘carry-over’ and ‘temporal’ effect of the treatment and to test the time effect of TN. Data analyses will be performed a statistician using Stata version 13 software.

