### Primary outcome measure

The study’s primary outcome is participant satisfaction (parent or adolescent). Cox’s IMCHB defines the concept of satisfaction with nursing care from the patient’s perspective. The degree to which nurses adapt their care to meet the specific needs of the parent, guardian, or child relates directly to satisfaction
[68]. Satisfaction is assessed using a mixed methods approach where both quantitative and qualitative data are gathered and analyzed separately, and then the different results are converged.

Client Satisfaction Questionnaire-8 (CSQ-8) is an 8-item version of the 18-item CSQ developed by Attkisson and Zwick
[76]. It was designed to measure global client satisfaction in service delivery and program evaluation; it is brief to administer, has good psychometric properties (as demonstrated in several studies), and has been translated and validated in several languages, including French
[77]. CSQ-8’s items are rated on a 4-point Likert-type scale giving a total score ranging between 8 (no satisfaction) and 32 (total satisfaction). This study’s primary quantitative comparison will be the proportion of subjects in the intervention group (TN) and the control group (standard practice) with total CSQ-8 scores ≥ 30, as well as comparison within subjects as measured by CSQ-8 at T0, T6, T12, T18, and T24.

Qualitative data will be collected via individualized semi-structured interviews (SSI) at the end of each study period (T12 and T24) to avoid any bias. SSI have been commonly used in evaluating health programs and are particularly useful for exploring people’s in-depth knowledge, experiences and understanding. They can supplement or substantiate other sources of data
[78]. Here, the objective of SSI will be to determine satisfaction with regards to affective support, health information, and support in decision-making received.

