### Sample size and power

In 2008, 113 newly diagnosed children were admitted to the study hospital’s pediatric rheumatology outpatient clinic. Of these, 48 were diagnosed with an inflammatory rheumatic diseases. Based on these numbers, it is anticipated that around 70 children will be admitted to the clinic in the 18-month screening period prior to enrolment into the study. If we consider that 80% of patients/parents will give consent to their participation, this would leave a pool of 56 families available for the two-year study period.

A power analysis was calculated based on the number of participants expected to complete the study, not the number recruited initially. If we consider a difference in the proportion of subjects in the two groups with a satisfaction score ≥30, e.g. 70% in TN versus 20% in the control group, then 23 subjects per group (total of 46 subjects) would be required to reach a power level of .90 for an alpha level of .05 (two-sided test). Effective strategies will be used to maintain the sample size. To compensate for an expected attrition rate of 20%, two groups of 28 subjects will be recruited (total of 56 subjects).

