#### Data screening and missing data

Prior to data analyses, data will be screened for the accuracy of the data file, missing data, outliers, and distribution. Cases with more than 20% of missing data will be excluded from analyses and missing data will be randomly replaced using the expectation maximization (EM) method. “EM forms a missing data correlation matrix by assuming the shape of a distribution…for the partially missing data and basing inferences about missing values on the likelihood under that distribution” (p. 63)
[88]. Normally distributed data and homogeneity of variance will be analyzed using parametric tests, and skewed data will be analyzed with the equivalent non-parametric tests.

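### The only powered comparison is a proportion (CSQ-8 of 30 or more), but the hypothesis-testing section names no method suited to it, and a skewness rule could change the analysis of the CSQ-8 score after the data are seen

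*Protocol article*

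**What the plan says.** Four sections of the protocol article bear on this.

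- **Primary outcome measure.** The "primary quantitative comparison will be the proportion of subjects in the intervention group (TN) and the control group" with a CSQ-8 total of 30 or more. The same sentence adds a second part: "as well as comparison within subjects as measured by CSQ-8 at T0, T6, T12, T18, and T24". The total runs from 8 to 32. No time point is fixed for the proportion.
- **Sample size and power.** The calculation uses only the proportion, "70% in TN versus 20% in the control group", with power 0.90 and two-sided alpha 0.05, and concludes that "23 subjects per group (total of 46 subjects) would be required".
- **Hypotheses testing.** "Data will be analyzed using mixed effect linear models to exclude any" carry-over and temporal effects, and to test the time effect of telenursing. Summaries are the mean and SD, and continuous variables are tested for normality.
- **Data screening and missing data.** "Normally distributed data and homogeneity of variance will be analyzed using parametric tests, and skewed data will be analyzed with the equivalent non-parametric tests". CSQ-8 is not exempted.

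The chi-square test is named once, at the start of Data analysis, in the paragraph that checks whether the two groups are alike on demographic variables and diagnosis.

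**The concern.** The endpoint that justifies the sample size is yes/no, while the named model and summaries are for a continuous response. The link between the power statement and the analysis is therefore missing for the one comparison that has a stated effect size.

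The score part has a different problem. It has a model, but a distribution check can override it. The crossover analysis has to handle period and carry-over, which is the reason the protocol gives for a mixed model. The usual rank tests do not carry those terms. If the switch operates, the primary score result comes from an analysis chosen after looking at the data and without the crossover structure. Participants and caregivers are not blinded, which makes one fixed analysis more important.

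At stake is whether the reported primary result matches the quantity that the trial was sized to detect.

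**Working it through.** **1. Reproduce the stated sample size.** Inputs from Sample size and power: p1 = 0.70, p2 = 0.20, difference d = 0.50, two-sided alpha 0.05 (z = 1.960), power 0.90 (z = 1.282). Mean proportion = 0.45.

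Uncorrected, per group:

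n = [1.960 × √(2 × 0.45 × 0.55) + 1.282 × √(0.70 × 0.30 + 0.20 × 0.80)]² / 0.50²
= [1.960 × 0.7036 + 1.282 × 0.6083]² / 0.25 = 18.6, so 19.

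With continuity correction:

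n' = (n/4) × [1 + √(1 + 4/(n·d))]² = (18.6/4) × [1 + √(1 + 4/(18.6 × 0.50))]² = 22.5, so **23 per group**.

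This is the protocol's figure. By exact enumeration, Fisher's test has power 0.913 with 23 per group and 0.890 with 22. The calculation behind the trial is thus a test of two independent proportions.

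**2. Set the powered comparison beside the named analyses.**

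| Part of the primary comparison | Effect and power stated? | Method named? |
|---|---|---|
| Proportion with CSQ-8 ≥ 30, telenursing vs control | Yes: 70% vs 20%, power 0.90 | None suited to a yes/no response |
| Within-subject CSQ-8 at T0, T6, T12, T18, T24 | No | Linear mixed model, or non-parametric tests if skewed |

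The part with a power statement has no fitting method. The part with a fitting method has no power statement, and its method can be replaced after inspection of the data. The 90% figure cannot be carried over to the score, because the protocol gives no mean difference or SD for it.

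**3. Could the switch operate for CSQ-8?** The score takes 25 values (8 to 32), and 30, 31 and 32 are the top three. If 70% of telenursing scores lie there, as the sample size assumes, a ceiling effect is plausible. It is not forced: 10% at 28, 20% at 29, 40% at 30, 20% at 31 and 10% at 32 also puts 70% at 30 or more and is symmetric. The switch is a real possibility, not a certainty.

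**4. Would a matching crossover test need more patients?** For a paired binary (McNemar-type) test with difference 0.50 and total discordance ψ, the number of pairs is

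n = [1.960 × √ψ + 1.282 × √(ψ − 0.25)]² / 0.25.

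The protocol gives no ψ, so the whole range compatible with 70% and 20% is shown. Period effects are ignored.

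| ψ | Meaning | Pairs needed | Power with 46 completers |
|---|---|---|---|
| 0.50 | smallest possible | 17 | above 0.999 |
| 0.62 = 0.7 × 0.8 + 0.3 × 0.2 | responses independent between periods | 22 | 0.999 |
| 0.90 | largest possible | 34 | 0.97 |

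A 20% loss from 56 leaves 44.8 rather than 46. With 45 completers the power in the last row is still 0.97.

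**The case against.** The strongest reply is that the protocol does not contradict itself outright. The primary comparison includes repeated CSQ-8 scores, for which a linear mixed model is a natural choice. The sentence naming that model speaks of data in general and does not say that the yes/no indicator goes into it. The protocol commits to comparing the proportions, and an analysis plan that is not shown may name the test. This stands in part. It does not remove the mismatch, because the section that sets out hypothesis testing names a model, and that model does not fit the only powered comparison.

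Four stronger readings are tempting, and the document does not support them:

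- *The powered comparison is never tested.* A reader might infer this, but the comparison is promised, and even a linear model on the 0/1 indicator would estimate a difference in proportions. What can be said is that no suited method is named.
- *Three incompatible analyses apply to one endpoint.* The skewness rule concerns skewed data and normality testing is limited to continuous variables. Neither replaces a test of a proportion. The competition is between two analyses of the score.
- *The score must be skewed under the plan's own figures.* The symmetric example in the working shows otherwise.
- *Unequal variances (0.21 and 0.16 on the 0/1 scale) spoil a linear model's standard error.* With equal allocation the pooled and unpooled variances of the difference coincide: 2 × [(0.21 + 0.16)/2]/n = (0.21 + 0.16)/n.

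**Conclusion.** The point holds in two limited parts. First, the sample size belongs to a test of two independent proportions, and the hypothesis-testing section assigns no method suited to that yes/no endpoint. Second, for the CSQ-8 score, the rule on skewed data lets the observed distribution decide whether the crossover structure is kept. The first follows directly from the text and the reproduced 23 per group. The second rests on a ceiling effect that is plausible for a scale capped at 32 but not established by the protocol.

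The consequence is a primary result that may not correspond to the powered quantity or may depend on an analysis chosen after the data are seen. It is not a shortage of patients: under the plan's own 70% and 20%, a matching paired test stays within the planned number of completers over the full range of discordance, if period effects are ignored.

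**What to change.** Before the CSQ-8 data are analysed, amend the analysis text as follows:

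1. Name the proportion with CSQ-8 of 30 or more, at one stated time point per period, as the primary comparison. The end of each period (T12 and T24) is an obvious choice within the existing schedule.
2. Assign it one crossover binary model, for example GEE logistic regression with robust standard errors and terms for treatment, period and sequence. Report the marginal risk difference with its 95% CI, since the sample size is stated in proportions.
3. Make the mixed model for the repeated CSQ-8 scores supportive.
4. Exempt CSQ-8 from the normality-triggered switch, so that no distribution check can change its analysis.

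The cost is analysis-plan wording and slightly more analysis work. It needs no extra patients, visits or questionnaires.

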### Statistical methods

#### Mixed methods analyses

The primary outcome of satisfaction, as measured using the CSQ and the interviews, will be analyzed using the triangulation design convergence model described by Creswell
[86]. This model is used for comparing results and corroborate quantitative results with qualitative findings. The quantitative and qualitative data will be analyzed separately, but the different results will be converged (by comparing and contrasting the results) for the interpretation of the findings. This method will provide valid and substantiated conclusions about the satisfaction outcome. Qualitative data analyses will be carried out using the content analysis method, including, a) identification of units of analysis, and b) analysis of content by developing categories using ATLAS.ti V6 computer software
[87].

#### Data screening and missing data

Prior to data analyses, data will be screened for the accuracy of the data file, missing data, outliers, and distribution. Cases with more than 20% of missing data will be excluded from analyses and missing data will be randomly replaced using the expectation maximization (EM) method. “EM forms a missing data correlation matrix by assuming the shape of a distribution…for the partially missing data and basing inferences about missing values on the likelihood under that distribution” (p. 63)
[88]. Normally distributed data and homogeneity of variance will be analyzed using parametric tests, and skewed data will be analyzed with the equivalent non-parametric tests.

#### Representativeness and bias

Demographic data and reasons for refusals to participate in the study, as well as those who are lost (withdraw, lost to follow-up, etc.…), will be compared to participants who remain in the study. Recruitment will be performed at the tertiary referral hospital for children with chronic rheumatic diseases in the Canton of Vaud, which will ensure the representativeness of the population of children with this condition and avoid referral bias. Furthermore, strategies to maximize the follow-up of study participants from both groups will be used. Finally, to minimize the risk for bias in self-reported satisfaction, participants will return their completed questionnaires in sealed envelopes addressed to the research team. Participants will also be informed that their satisfaction levels will be confidential, will not be shared with their caregivers, and will not interfere with the quantity and quality of care provided.

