### Data collection

Data will be collected at different time points over the 24-month study period (see Figure 
2). Participants switch to the other allocated group immediately after completion of study period 1. In this particular study, a wash-out period is considered unnecessary as the next measurement of satisfaction takes place six months after the start of period 2; this provides sufficient time to eliminate any residual effects of the treatment allocated in period 1. Data collection will be shared between the telephone nurses, a research assistant (nurse), and a physician. Telephone nurses will record the frequency, duration, and nature of all calls made and received. Records of each telephone call will be taken throughout data collection periods 1 and 2 (two years for each participant).The choice of the number of data collection points and the study timespan is based on theoretical and practical considerations
[74]. For practical reasons, patients will be enrolled in the first week of the month; face-to-face consultation baseline data (demographics, health status, and satisfaction) will be collected at this time (T0). Collection points occur every three months for assessments of disease activity and health status (T3, T6, T9, T12, T15, T18, T21, and T24) and every six months for the satisfaction questionnaire (T6, T12, T18, and T24).

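### The planned comparison of lost families omits satisfaction, and nothing is measured at exit, so loss related to dissatisfaction is not adequately examined

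*Protocol article*

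**What the plan says.** Under Representativeness and bias, the check on non-participants and leavers is described as "Demographic data and reasons for refusals to participate in the study, as well as those who are lost", set against those who stay. No other comparison variable is named. The same section plans follow-up strategies in both groups and confidential return of questionnaires in sealed envelopes.

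The satisfaction schedule is fixed. Data collection states that "baseline data (demographics, health status, and satisfaction) will be collected at this time (T0" and then gives "every six months for the satisfaction questionnaire (T6, T12, T18, and T24". Primary outcome measure compares the proportions "with total CSQ-8 scores ≥ 30, as well as comparison within subjects as measured by CSQ-8 at T0, T6, T12, T18, and T24". It adds: "Qualitative data will be collected via individualized semi-structured interviews (SSI) at the end of each study period (T12 and T24) to avoid any bias". Neither section describes a measurement when a family stops early.

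Sample size and power assumes "70% in TN versus 20% in the control group" and anticipates loss: "To compensate for an expected attrition rate of 20" per cent, 28 are recruited per group (56 in all).

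Three other places bear on the point. Hypotheses testing promises an intent-to-treat analysis with mixed effect linear models. Data screening and missing data drops any case missing more than 20% of its data and fills in the rest by expectation maximization. Randomization and allocation of treatment acknowledges that blinding of participants and caregivers is not feasible.

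**The concern.** Satisfaction with a service is the endpoint, and dissatisfaction with that service is a plausible reason to leave it or the study. Missingness may then depend on the outcome itself. Families who leave could match those who stay on age, education and diagnosis and still differ on the proportion scoring 30 or more. Recorded reasons help, but a reason is not a CSQ-8 score and cannot enter that proportion.

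The interviews do not fill the gap. They are taken from families still present at T12 or T24. The section on mixed methods analyses uses them to corroborate the questionnaire result. If both sources lose the same families, their agreement says nothing about the selection. Whatever bias the end-of-period timing was meant to avoid, it does not protect against this one.

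At stake is whether a reader of the results could tell if the difference in the primary proportion was shaped by who stayed.

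**Working it through.** **The plan's own figure.** The inputs are 70% versus 20%, and enough subjects to "reach a power level of .90 for an alpha level of .05 (two-sided test"). The pooled proportion is 0.45.

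- Without continuity correction: n = [1.96 × √(2 × 0.45 × 0.55) + 1.2816 × √(0.70 × 0.30 + 0.20 × 0.80)]² / 0.50² = (1.379 + 0.780)² / 0.25 ≈ 18.6, so 19 per group.
- With continuity correction: (18.6 / 4) × [1 + √(1 + 4 / (18.6 × 0.50))]² ≈ 22.5, so 23 per group.

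The stated 23 is reproduced. The expected loss is 0.20 × 56 = 11.2 families.

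**What a leaver contributes under the fixed schedule.** The right-hand column is an assumption: it reads the 20% missing-data rule over the five CSQ-8 time points.

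| Family leaves | CSQ-8 held | Interview held | CSQ-8 missing |
|---|---|---|---|
| Month 5 | T0 | none | 4/5 = 80%, excluded |
| Month 11 | T0, T6 | none | 3/5 = 60%, excluded |
| Just after T12 | T0, T6, T12 | T12 | 2/5 = 40%, excluded |
| Just after T18 | T0, T6, T12, T18 | T12 | 1/5 = 20%, kept |

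On that reading, the first three families' scores enter neither the analysis nor the stated comparison of leavers, although the scores exist.

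**How far selective loss could move the difference.** The documents give no loss by condition or by satisfaction, so these are assumed scenarios. They treat the arms as parallel with 28 each and a true 70% versus 20%. Satisfied families number 0.70 × 28 = 19.6 (TN) and 0.20 × 28 = 5.6 (control). Dissatisfied families number 8.4 and 22.4. Every leaver is taken as dissatisfied, so the observed proportion is satisfied / (28 − lost).

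- *One common departure rate among dissatisfied families, 11.2 lost in all.* The rate is 11.2 / 30.8 = 36.4%. TN loses 3.05: 19.6 / 24.95 = 78.6%. Control loses 8.15: 5.6 / 19.85 = 28.2%. The difference is 50.4 points against a true 50.
- *20% lost from TN only.* 19.6 / 22.4 = 87.5% versus 20%: 67.5 points.
- *20% lost from control only.* 70% versus 5.6 / 22.4 = 25%: 45 points.
- *Extremes with 11.2 lost in all.* TN 30% and control 10%: 19.6 / 19.6 = 100% versus 5.6 / 25.2 = 22.2%, or 77.8 points. TN 0% and control 40%: 70% versus 5.6 / 16.8 = 33.3%, or 36.7 points.

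**With no true effect** (45% satisfied in both arms, an assumed value), equal loss gives no bias. Loss of 30% versus 10% gives 0.45 / 0.70 − 0.45 / 0.90 = 64.3% − 50.0% = 14.3 points, favouring the arm that lost more.

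**The case against.** The strongest reply is that this is a normal sentence in a condensed article. It does not say demographics and reasons are the only things to be compared, and fuller work on informative loss is commonly left to the full protocol or analysis plan. Fixed six-monthly questionnaires and end-of-period interviews are standard. That much stands: the schedule is not an error in itself. But the article does name its comparison variables. They leave out the endpoint, which is held from T0.

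A reader might infer that loss through dissatisfaction would go entirely unseen. The documents do not support that. Reasons are collected, and Study protocol compliance monitoring has information gathered when TN calls or appointments are missed. Every enrolled family is due a T0 score, and those who leave after month 6 should have a later one. Nor does the article say that refusers and leavers will be merged. It only names them in one sentence.

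A reader might also infer that 20% loss of dissatisfied families in each condition inflates the effect to 87.5% − 25% = 62.5 points. That scenario is not neutral. It needs 5.6 / 8.4 = 67% of dissatisfied TN families to leave but only 5.6 / 22.4 = 25% of dissatisfied controls. With one common rate the bias almost vanishes. The parallel-arm arithmetic also ignores the crossover: a family lost in period 2 has already supplied its period 1 data, and the 20% covers the whole study.

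**Conclusion.** The point holds as an inadequacy of the stated check, not as a demonstrated bias. In an unblinded trial with satisfaction as primary outcome and about 11 of 56 families expected to leave, the named comparison omits satisfaction and condition at departure. No score is sought at exit, and the interviews cannot reveal the selection.

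The direction and size of any bias are unknown. Under the assumptions shown (parallel arms, true 70% versus 20%, every leaver dissatisfied), the difference is about 50 points with a common departure rate, 67.5 with 20% loss in TN only and 45 with 20% loss in control only. The extremes for 11.2 families lost are 36.7 and 77.8. No figure in the documents says which case applies, or that all leavers would be dissatisfied.

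A change is worth making because the first part uses data already collected and the second is small.

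**What to change.** 1. **Representativeness and bias.** Also compare leavers with those who stay on T0 CSQ-8, last available CSQ-8 and disease activity. Report this by sequence and by the condition the family was in at departure, and report refusers separately. No new data are needed, and it can be added before analysis.

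2. **Data collection and Primary outcome measure.** Ask any family that stops early, and is willing, to return one CSQ-8 by the existing sealed-envelope route, referring to the condition they were in. Use it as that period's assessment in a stated sensitivity analysis. An exit interview can be offered but is optional.

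3. **Data screening and missing data against Hypotheses testing.** Reconcile the exclusion of cases missing more than 20% of their data with the intent-to-treat statement, so that leavers' existing CSQ-8 scores are kept. The mixed model can use incomplete series.

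Part 2 needs a short amendment and one mailed 8-item form for about 11 families. Some leavers will decline, and exit scores will fall at non-standard times, which is why they belong in a sensitivity analysis. Recruitment began in August 2011 and follow-up ends in August 2014, so families already lost would have to be recontacted, subject to their right to withdraw. Otherwise the form applies only to later departures.
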